#### Users’ feedback, feasibility, usability

In addition, completion, usability and satisfaction of the program will be assessed for utilization and a feasibility test. The intervention completion rate of each group will be assessed. Usability of the e-SMARPP website will be assessed using the Web Usability Scale (WUS) [49]. The WUS consist of 21 items measured on a 5-point scale and seven subscales: ease of use, ease in understanding structure, ease in reading, response speed, favorable, helpfulness and credibility. The subscale average score will be calculated, higher score indicates higher website usability. Usability of e-SMARPP contents will be assessed using original questionnaires. Example of questions include, “What is the most useful/unuseful content?”, “Are videos easy to use? (with options ranging from very easy to very difficult)” and “How long does it take to complete one exercise?”. Perceived program satisfaction will be assessed using the Client Satisfaction Questionnaire 8-item version (CSQ-8) [50]. CSQ-8 consists of eight items measured on a 4-point scale. A higher score indicates a higher satisfaction with service use.

#### Participant characteristics

At the baseline assessment, sociodemographic information will be gathered including age, sex, marital status, cohabitation status, educational history, employment status and Internet use (use days per week, hours per day and main devices to access).

Information about history of drug use will be also asked. The primary problematic drug will be asked. Drug use in the past 28 days will be collected using the self-monitoring calendar based on the TLFB method. In addition, we assess first-abused drug, onset age of any drug abuse and the primary drug abuse, polydrug abuse (yes/no), abstinence duration calculated from the day when they last used a drug, experience of past arrest (yes/no), past experience in a correctional facilities (yes/no), and self-reported psychiatric comorbidity with an option to select a diagnosis based on the International Classification of Diseases-10. Similarly, we evaluate history of treatment in several ways: duration of psychiatry outpatient ward, number of psychiatry hospitalization, specialized behavioral treatment for drug problems in the past (yes/no), and self-help group use (yes/no).

In order to assess severity of drug use problems, we use the Japanese version of the Drug Abuse Screening Test (DAST-20), which consists of 20 binary items [51, 52]. All items will ask participants’ drug use condition in the past year. Total score ranges from 0 to 20 and a high score represents a severe condition. The cutoff score for drug use disorders is suggested as 5/6 with maximum sensitivity and specificity [53–55], although an optimal cutoff score has not confirmed in different populations and culture. It is also suggested that a score of 16 or greater be considered to indicate a very severe dependence condition [56]. Furthermore, the Kessler-6 scale consisting of six items measured on a 5-point scale will be used to assess psychological distress [57, 58]. A total score ranging from 0 to 24 and a high score indicates severe distress. The optimal cut-off point is considered 4/5 for a mood and anxiety disorder [59].

### Sample size

Sample size is assumed for two primary outcome variables (relapse risk and the longest duration of abstinence) to detect a medium effect size of *d* = 0.4 based on previous studies for drug users. As for the first primary outcome (relapse risk), the effect size between pre and post intervention was *d* = 0.39 in a study conducting a relapse prevention program in Japan [60]. On another primary outcome (the longest duration of abstinence), the effect size between the intervention group and control group after the intervention was reported as *d* = 0.45 in a study conducting for computer-assisted cognitive behavioral therapy [19]. We estimated a sample size of 100 per group (total 200), assuming α = 0.05 and a power (1 - β) = 0.08. Attrition rate and non-completion rate was reported as relatively high (about 10–45 %) in previous studies of computer-assisted and web-based intervention for drug users [11, 19, 61]. However, we did not include additional samples because we expect a low attrition rate because all the participants will be outpatients motivated to seek treatment and we will send email reminders to follow up.

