### Statistical analysis

#### Primary analysis

The primary analysis for the SRRS score will be on an intention-to-treat basis, using mixed-effect models. We will use all obtained data at the 2, 5 and 8 months assessment without imputation, assuming the missing mechanism will be at random given observed data within the groups. We will include the following variables as fixed effects: the group, time, the baseline scores and the interaction of group and time. Time will be coded as months after the baseline assessment, giving values of 0, 2, 5 and 8. We will also include random effects of participants for intercept and time. The effect of the intervention will be assessed by a test of hypothesis that a time and group interaction equals 0. To help interpretation in terms of effect size, Cohen’s *d* between groups and 95 % confidence intervals will be calculated at each assessment point; the values of 0.2, 0.5 and 0.8 are considered as small, medium and large effect, respectively [62]. The longest consecutive abstinent days from the primary abused drug during intervention will be compared using *t*-test. Also, we will calculate a Cohen’s *d* for the longest consecutive abstinent days.

When there are significant differences in both of the two primary outcomes between groups with a level of 5 % in the two-sided test, the intervention will be considered effective. Analyses will be conducted using SPSS Statistics Ver. 22.

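### Power is printed as 0.08; corrected to 0.80 it describes one outcome with no loss, while the trial's conclusion needs both primary outcomes to be significant

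*Protocol article*

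**What the plan says.** The Sample size section says that the trial is sized for both primary outcomes, relapse risk (SRRS) and longest abstinence, "to detect a medium effect size of *d* = 0.4 based on previous studies for drug users". The supporting effects are d = 0.39 for relapse risk, a pre-post change, and d = 0.45 for longest abstinence, a difference between groups. The result is given as "We estimated a sample size of 100 per group (total 200), assuming" a 5% alpha, with the power printed as "a power (1 - β) = 0.08".

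On loss, the same section notes: "Attrition rate and non-completion rate was reported as relatively high", at roughly 10% to 45% in comparable trials. It continues: "However, we did not include additional samples because we expect a low attrition rate". The reasons given are that participants are outpatients motivated to seek treatment and that reminders will be sent.

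The decision rule is in the Primary analysis section. The program is to be judged effective "When there are significant differences in both of the two primary outcomes between groups"; each test is two-sided at 5%. There the SRRS is tested by the group-by-time interaction in a mixed-effects model, and longest abstinence by a t-test. The article gives neither a joint power nor a correlation between the two outcomes.

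**The concern.** Two things do not fit together. First, the printed power cannot be the one used, because it does not lead to 100 per group. Second, once it is read as 0.80, the number is the usual size for a single two-sample comparison, yet success is defined by two tests that must both be passed. The chance of passing both cannot exceed the chance of passing either one, so a calculation that gives about 0.80 for one outcome leaves the conclusion with less.

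The stake is interpretation. The Discussion section expects the design to give conclusive results. If the true effects are as planned, a miss on at least one outcome is considerably more probable than a reader of 0.80 would suppose, and a split or null result would be weaker evidence against the program. The absence of any allowance for loss adds to this, since 100 per group leaves no margin.

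**Working it through.** **Inputs from the Sample size and Primary analysis sections.** d = 0.4 on both outcomes; two-sided alpha 0.05 for each; 100 per group, 1:1; both outcomes must be significant; no participants added for loss; cited loss 10% to 45%. **Not in the document:** the correlation r between the two test statistics. I assume values from 0 to 0.9 and show the results.

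**Step 1: reproduce the plan's N.** n per group = 2 × (z for 0.975 + z for power)² / d².

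- Power 0.80: 2 × (1.960 + 0.842)² / 0.16 = 98.1, so 99. By the noncentral t distribution, power is 0.7997 at 99 and 0.804 at 100.
- Power 0.08: 2 × (1.960 − 1.405)² / 0.16 = 3.85, so 4.
- Power 0.80 with a one-sided test: 78.

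Only 0.80, two-sided, for one outcome with everyone analysed, gives the stated 100.

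**Step 2: power for one outcome.** The test statistic has mean d × √(n/2) = 0.4 × √50 = 2.83. Power is Φ(2.83 − 1.96) = Φ(0.87) = 0.807 by the normal approximation, against 0.804 by noncentral t.

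**Step 3: power for both.** Joint power = P(Z1 > 1.96 and Z2 > 1.96), bivariate normal with means d × √(n/2) and correlation r. At r = 0 it is 0.8074² = 0.652.

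**Step 4: add loss.** 10% loss leaves 90 per group; 45% leaves 55. The calculation removes each lost participant from both analyses.

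| Analysed per group | One outcome (noncentral t) | Both, r = 0 | Both, r = 0.5 | Both, r = 0.9 |
|---|---|---|---|---|
| 100 | 0.804 | 0.652 | 0.697 | 0.759 |
| 90 | 0.761 | 0.586 | 0.640 | 0.710 |
| 55 | 0.547 | 0.308 | 0.390 | 0.484 |

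**Step 5: use the two cited effects instead of 0.4.** With 0.39 and 0.45 at 100 per group, the single powers by normal approximation are 0.787 and 0.889. Joint power is 0.787 × 0.889 = 0.700 at r = 0 and 0.735 at r = 0.5.

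**Step 6: chance of a miss at d = 0.4 with complete data.** At least one outcome is missed with probability 1 − 0.652 = 0.35 (r = 0), 1 − 0.697 = 0.30 (r = 0.5) or 1 − 0.759 = 0.24 (r = 0.9). Exactly one is missed with probability 2 × (0.807 − 0.652) = 0.31 at r = 0, or 2 × (0.807 − 0.697) = 0.22 at r = 0.5.

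**The case against.** Several points on the other side are sound.

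- **The 0.08 is a misprint.** Step 1 shows that 0.80 was used. A reader might infer that the trial was designed with 8% power; the stated N rules that out.
- **The SRRS is not tested by a t-test.** Its test is a group-by-time interaction with baseline score, random intercept and random time. The power of that test depends on variance components and a trajectory that the article does not give, and it could be higher or lower than the t-test figure. The one SRRS effect cited is pre-post. This stands: neither 0.80 for each outcome nor any single joint figure can be asserted as the design's true power. It does not rescue 0.80 for the decision rule. Whatever the SRRS power is, joint power cannot exceed that of the abstinence t-test, which is 0.80 at the planning effect with complete data.
- **The correlation is unknown.** This stands too. A reader might take 0.65 to 0.70 as the answer, but that rests on assuming a correlation between 0 and 0.5. At 0.9 the figure is 0.76.
- **The 45% bound is harsh.** A reader might conclude that power falls to 0.31 at the attrition the plan cites. The document does not support that. The cited range mixes attrition with non-completion, and not completing the program removes nobody from an intention-to-treat analysis. The SRRS model uses all obtained data, and the abstinence outcome covers only the 56-day intervention, so later dropout does not affect it. The figures at 45% are a worst case.
- **Loss was considered.** The plan discloses the range, explains its optimism, and provides for reminders, a postcard and payment per assessment. That is a judgement rather than an oversight, but its consequence for power should be shown.
- **The rule is statistically valid.** Requiring both outcomes does not inflate type I error; the cost is in power. Nor does the protocol say that one miss will be read as proof of no effect, and it reports effect sizes for both outcomes.

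**Conclusion.** Wrong as written. The printed power is incorrect, and the corrected value of 0.80 does not describe the trial's own success rule. On the plan's t-test basis, with d = 0.4 on both outcomes and complete data, joint power is about 0.65, 0.70 or 0.76 at assumed correlations of 0, 0.5 and 0.9. With the two cited effects it is about 0.70 to 0.735 at correlations of 0 to 0.5. At 10% loss, single-outcome power is 0.76 and joint power about 0.59 to 0.71 over correlations of 0 to 0.9; the worst case of 45% loss from both analyses gives about 0.31 to 0.48.

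The direction is firm: for two tests each powered at about 0.80, the chance of passing both is lower unless the tests are perfectly correlated. The exact size is not firm, because it depends on an unstated correlation and on treating the SRRS interaction test as if it were a two-group comparison.

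**What to change.** Keep N = 200, the outcomes and the success rule. In the Sample size section:

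1. Change 0.08 to 0.80 and label it as the power of a single two-group comparison at d = 0.4, two-sided 5%, with all 200 participants analysed.
2. Add the power for the rule that both outcomes must be significant: about 0.65, 0.70 or 0.76 at correlations of 0, 0.5 and 0.9 with complete data, stating that the correlation is assumed.
3. State the effect of loss: about 0.59 to 0.71 at 10% over the same correlations. If 45% is shown (0.31 to 0.48), call it a worst case and say why.
4. Say that the SRRS is tested by a group-by-time interaction and that its cited effect of 0.39 is pre-post, so the power of that test is not established by this calculation.

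The cost is a less favourable stated figure. No participants are added and no analysis changes.

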### Statistical analysis

#### Primary analysis

The primary analysis for the SRRS score will be on an intention-to-treat basis, using mixed-effect models. We will use all obtained data at the 2, 5 and 8 months assessment without imputation, assuming the missing mechanism will be at random given observed data within the groups. We will include the following variables as fixed effects: the group, time, the baseline scores and the interaction of group and time. Time will be coded as months after the baseline assessment, giving values of 0, 2, 5 and 8. We will also include random effects of participants for intercept and time. The effect of the intervention will be assessed by a test of hypothesis that a time and group interaction equals 0. To help interpretation in terms of effect size, Cohen’s *d* between groups and 95 % confidence intervals will be calculated at each assessment point; the values of 0.2, 0.5 and 0.8 are considered as small, medium and large effect, respectively [62]. The longest consecutive abstinent days from the primary abused drug during intervention will be compared using *t*-test. Also, we will calculate a Cohen’s *d* for the longest consecutive abstinent days.

When there are significant differences in both of the two primary outcomes between groups with a level of 5 % in the two-sided test, the intervention will be considered effective. Analyses will be conducted using SPSS Statistics Ver. 22.

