### Objectives and hypotheses

The aim of this study is to examine the effects of a web-based cognitive behavioral relapse prevention program, revised as e-SMARPP, among Japanese psychiatric outpatients with methamphetamine and other drugs use problems with a multicenter randomized controlled trial (RCT) design. The primary hypothesis is that participants assigned to e-SMARPP will have reduced relapse risk and maintain a longer duration of consecutive abstinence (days) from a primary abused drug during the intervention compared to those who were randomized to self-monitoring only. The secondary hypothesis is that participants in the e-SMARPP group will report positive changes in motivation to change, self-efficacy for drug craving, abstinent days in the past 28 or 56 days (percentages and differences in change: pre-post), quality of life, sense of coherence, cost of alcohol and drug, retention of treatment, use of self-help group and psychiatric medical cost. In addition, completion, usability and satisfaction of the program will be assessed for utilization and feasibility test. This article describes the study protocol according to SPIRIT guidelines [27].

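### The SRRS co-primary is decided by a linear group-by-time slope, not the level difference that was hypothesised and powered, and the model paragraph contradicts itself on whether baseline is an outcome

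*Protocol article*

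**What the plan says.** All of the following is in the Protocol article. Under Primary analysis, the SRRS model is a mixed-effect model. On the data: "We will use all obtained data at the 2, 5 and 8 months assessment without imputation". On the fixed effects: "We will include the following variables as fixed effects: the group, time, the baseline scores and the interaction of group and time". On the coding of time: "Time will be coded as months after the baseline assessment, giving values of 0, 2, 5 and 8". On the random part: "We will also include random effects of participants for intercept and time". The deciding test is then named: "The effect of the intervention will be assessed by a test of hypothesis that a time and group interaction equals 0". Cohen's d with a 95% confidence interval at each assessment is added as an aid to interpretation.

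The success rule in the same section begins: "When there are significant differences in both of the two primary outcomes between groups with a level of 5 % in the two-sided test". It names no direction.

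Under Objectives and hypotheses, e-SMARPP participants "will have reduced relapse risk and maintain a longer duration of consecutive abstinence (days) from a primary abused drug during the intervention", compared with self-monitoring only. Under Sample size, 100 per group is set to detect d = 0.4 on both primary outcomes. Under Intervention group, the program runs for 8 weeks, so the 5- and 8-month assessments fall after it ends.

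**The concern.** Because time is a number of months with a participant-level slope, the interaction is one coefficient: the difference between arms in the straight-line rate of change. An 8-week program would plausibly produce its effect by the 2-month visit, after which the effect holds or wears off. A slope test answers a different question from whether relapse risk is lower with e-SMARPP.

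How badly it answers depends on a point the section leaves contradictory. The data and fixed-effects sentences treat baseline as a covariate and the 2-, 5- and 8-month scores as outcomes. The time value 0 has a use only if baseline scores are also outcome rows, and baseline would then sit on both sides of the model. The two readings give different answers for the same true effect.

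SRRS must be significant for the intervention to be called effective, so this test can decide the trial's conclusion.

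**Working it through.** **Plan's own figure.** Two-group comparison of means, d = 0.4, two-sided 5%, 80% power: n = 2 × (1.960 + 0.842)² / 0.4² = 98.1, so 99 per group; 100 per group gives 80.7%. The stated 100 is reproduced as a comparison of levels. (The printed power of 0.08 is evidently 0.80 and is a separate misprint.)

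**Inputs.** From the documents: 100 per arm, visits at 0, 2, 5 and 8 months, d = 0.4, two-sided 5%. Assumed, because not given: unit SD, no attrition, and three correlation structures: (i) equal correlation 0.5, (ii) equal correlation 0.7, (iii) correlation decaying as 0.7 per 3 months. Effects are e-SMARPP minus control, so negative means benefit. Power = Φ(|z| − 1.96) plus the negligible opposite tail, with z from generalised least squares.

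**Reading A: outcomes at 2, 5 and 8 months, baseline as covariate.** Mean time is 5; sum of squared deviations is 9 + 0 + 9 = 18. Under (i), conditioning on baseline gives variance 1 − 0.25 = 0.75 and covariance 0.5 − 0.25 = 0.25, difference 0.50. Standard error of the slope difference = √(2/100 × 0.50/18) = 0.0236. Under (ii) the difference is 0.51 − 0.21 = 0.30 and the standard error is 0.0183.
- Sustained (−0.4, −0.4, −0.4): slope = (−3 × −0.4 + 3 × −0.4)/18 = 0. Rejection is 5% under every structure, and still 5% for a sustained 0.8. The benefit lies in the group main effect, which is not tested.
- Fading (−0.4, −0.2, −0.1): slope = (1.2 − 0.3)/18 = +0.05 per month. |z| = 2.12, 2.74 and 2.31 under (i), (ii) and (iii); rejection 56%, 78% and 64%. The positive sign means the arms converge.

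**Reading B: baseline rows added as outcomes.** Mean time is 3.75; sum of squared deviations is 14.06 + 3.06 + 1.56 + 18.06 = 36.75 (rounded terms). Standard errors are √(0.02 × 0.50/36.75) = 0.0165 under (i) and √(0.02 × 0.30/36.75) = 0.0128 under (ii).
- Sustained: slope = −0.4 × (−1.75 + 1.25 + 4.25)/36.75 = −0.041. z = −2.47 and −3.19; power 70% and 89%. Under (iii), 71%.
- Fading 0.4/0.2/0.1: slope = (0.70 − 0.25 − 0.425)/36.75 = 0.0007. Power 5%, 5% and 9%.
- Fading 0.4/0.3/0.2: slope = (0.70 − 0.375 − 0.85)/36.75 = −0.0143. Power 14%, 20% and 23%.

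Letting the random-slope SD range from 0 to 0.05 per month widens the sustained-effect power under reading B to 62–89%.

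**Level test: baseline-adjusted average over 2, 5 and 8 months.** Under (i), standard error = √(0.02 × (0.75 + 2 × 0.25)/3) = 0.0913. Under (ii), √(0.02 × (0.51 + 2 × 0.21)/3) = 0.0787.
- Sustained 0.4: z = 4.38 and 5.08; power 99% or more, also under (iii).
- Fading 0.4/0.2/0.1, average 0.7/3 = 0.233: z = 2.56 and 2.96; power 72% and 84%. Under (iii), 72%.

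| True effect at 2/5/8 months | Slope test, reading A | Slope test, reading B | Average level difference |
|---|---|---|---|
| 0.4/0.4/0.4 | 5% | 70–89% | 99% or more |
| 0.4/0.2/0.1 | 56–78%, converging sign | 5–9% | 72–84% |

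**The case against.** The strongest reply is that the time value 0 shows baseline rows are meant to enter. A group-by-time test on all four assessments is then conventional, and power for a sustained 0.4 is close to plan. The sentence about 2, 5 and 8 months can be read as being about missing data. This stands in part: a reader might infer that the planned test is always blind to a sustained benefit, and the documents do not support that. It is true only under reading A. But the listed baseline covariate points to reading A, the text does not settle the matter, and reading B still does poorly when the effect fades.

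A reader might also infer that a fading SRRS effect alone could make the trial positive. It could not. The abstinence t-test must also be significant, and under reading B the 0.4/0.2/0.1 pattern is rarely significant. In that pattern e-SMARPP is still better at every visit, the hypothesis does give a direction, and Cohen's d at each visit would show the convergence. What remains is narrower: under reading A, an interaction of the converging sign meets the SRRS half of a rule that states no direction.

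Nor should the hypothesis be read as fixing SRRS to the treatment period. The phrase on the intervention period most naturally belongs to abstinence, and SRRS is listed as primary at all four assessments. Follow-up is therefore within the design, and nothing makes 2 months the decisive visit. The source cited for the SRRS effect size is a pre-post d of 0.39, not a between-group one; the sample size nevertheless reproduces only as a two-group comparison of means at 0.4.

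**Conclusion.** The point holds in conditional form. The deciding SRRS test is a slope difference, while the hypothesis and the sample size concern a level difference, and the section contradicts itself on the role of baseline. For a sustained d = 0.4 the chance of a significant SRRS result is 5% or about 70–89%, depending on that unresolved choice. At 5%, the chance of overall trial success is also at most 5%, because both co-primaries are required. Fading benefits are either significant with a converging sign (56–78% for 0.4/0.2/0.1, reading A) or mostly missed (5–23% across the two fading patterns, reading B).

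The zero slope and 5% rejection under reading A follow from the design and need no correlation assumption. The other percentages rest on unit SD, no attrition and the assumed correlations. Neither the descriptive Cohen's d nor the inverse-probability-weighted sensitivity analysis, which addresses missingness and the definition of abstinence, changes the deciding test.

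**What to change.** Before the group variable is unmasked, amend the Primary analysis section as follows.

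1. Use the 2-, 5- and 8-month SRRS scores as outcomes and baseline SRRS as a covariate only. Delete the time value 0.
2. Treat visit as categorical, with group, visit and group-by-visit terms.
3. Make the primary test one prespecified baseline-adjusted group difference: the average over the three visits, or one named visit. Report the remaining visit-specific differences as secondary.
4. State that success requires both co-primary differences to favour e-SMARPP.

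The choice between the average and a named visit is a choice of estimand, which the sponsor must make and record; the documents do not single out one visit.

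The cost is a change of wording plus that decision. No additional participants or data are needed. The downside is that the slope comparison becomes secondary, so a claim about diverging trajectories would no longer be confirmatory.

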### Participants and setting

The participants are recruited from five psychiatric hospitals and one clinic (National Center of Neurology and psychiatry, Saitama Psychiatric Medical Center, Kanagawa Psychiatric Center, Okayama Psychiatric Medical Center, Tokyo Metropolitan Matsuzawa Hospital and APARI clinic) that provides treatment for people with substance use disorder in Japan. The inclusion criteria are: (1) outpatients who were diagnosed with substance use disorder assessed by DSM-5 (psychoactive substances other than alcohol and tobacco), (2) those who used a primary abused drug in the past year and (3) those with access to the Internet via PC, smartphone or tablet computer and can exchange e-mail. The exclusion criteria are: (1) patients with severe physical diseases, (2) patients with high suicide risk, (3) patients with severe symptoms of substance-induced psychotic disorder, (4) patients with impaired cognitive function and (5) those who judged ineligible to participate in the study by a psychiatrist. We include various types of participants (form of drugs, previous and current receiving treatment for drug dependence, psychiatric comorbidity, pharmacotherapy and sexual orientation) because we will test adaptation of e-SMARPP to various drug users in a secondary analysis.

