### Randomization and blinding

Staff of recruiting institutions will recruit outpatients who meet inclusion criteria. Eligible participants will be informed that they will be allocated to either of the two groups. After baseline assessment, they will be randomly assigned to either of the two groups using the method of permuted block, with random block size of four, and they will be informed their assigned group by the first author (AT). Randomization will be stratified by institution. The computer-generated allocation list was made by an independent researcher (YM) and concealed to other researchers and participants until the time of assignment. The enrollment is conducted by the first author (AT) and the intervention starts immediately. Researchers and staff who work for recruiting institutions will be blinded. In addition, an independent researcher (YM) who will not analyze data will download data from the e-SMARPP database and an independent research staff person will mask the group variable before analysis, then researchers (AT and [name]) will analyze data that is blinded to the group variable.

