**Fig. 4 Fig4:**
[figure not shown]
Screenshot of self-monitoring calendar

A self-monitoring calendar is used as a measure to assess drug use for a period of 28-days before the baseline and for follow-up assessments like the Timeline Followback (TLFB) method [28, 29]. Web-based versions of the TLFB methods have been developed and adapted to various substances with good reliability and validity [30–32] and have been used in some intervention studies [11, 19–21].

e-SMARPP is equipped with some automated functions for participants, including progress tracking and a notification e-mail when they receive feedback. In the notification e-mails, a related webpage link is shown and users can access the webpage directly. For example, users can view the feedback comment webpage directly after they click the link in the notification e-mail. Additionally, for researchers who registered on e-SMARPP, a notification e-mail will be sent when participants submit an exercise, diary and questionnaire.

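### The abstinence co-primary is tested without adjusting for baseline abstinence or for the stratifying institution; the t-test is valid but gives up precision that data already collected could supply.

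*Protocol article*

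**What the plan says.** All references are to the protocol article.

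- **Abstinence co-primary (Primary analysis).** "The longest consecutive abstinent days from the primary abused drug during intervention will be compared using" a t-test, with a Cohen's d alongside. No covariate is named.
- **SRRS co-primary (Primary analysis).** "We will include the following variables as fixed effects: the group, time, the baseline scores and the interaction of group and time". The random effects are participant intercept and time, and the test is of the group-by-time interaction. This model adjusts for its own baseline but does not contain institution.
- **Design (Randomization and blinding).** "Randomization will be stratified by institution", in permuted blocks of four. Participants and setting lists six institutions.
- **Population (Participants and setting).** Eligibility takes in "those who used a primary abused drug in the past year". The Subgroup analysis section divides participants by baseline abstinence into under 1, 1-6 and 7-12 months.
- **Baseline data.** "A self-monitoring calendar is used as a measure to assess drug use for a period of 28-days before the baseline", and Participant characteristics adds an abstinence duration counted from the last use of a drug.
- **Success rule (Primary analysis).** The intervention counts as effective "When there are significant differences in both of the two primary outcomes between groups with a level of 5 % in the two-sided test".

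**The concern.** The outcome is bounded at 56 days. Someone already abstinent for many months will plausibly score at or near 56, while a frequent user will score near 0. Much of the spread in the outcome may therefore reflect where participants started. A t-test leaves that spread in the error term, and any chance difference between arms in baseline abstinence partly carries over into the estimate.

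The protocol treats baseline values differently elsewhere. The SRRS model adjusts for its baseline, a secondary outcome is change in abstinent days from baseline, and the subgroup plan uses baseline abstinence duration. Only this co-primary test ignores it.

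Both co-primaries must be significant, so the chance of overall success cannot exceed the power of the weaker one. Precision given up here limits the whole trial.

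**Working it through.** **Inputs from the protocol.** d = 0.4; two-sided 5%; 1:1 allocation; 100 per arm; no allowance for attrition; six institutions; blocks of four. Sample size prints "a power (1 - β) = 0.08".

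**Inputs assumed.** The protocol gives neither the correlation r between baseline abstinence and the outcome nor the intraclass correlation (ICC) for institution. The ranges used are r = 0.3-0.6 and ICC = 0.01-0.10.

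**1. Reproducing the stated size.** With SD = 1, power = Φ(d / √(2/n) − 1.96). At n = 100, √(2/100) = 0.1414, 0.4/0.1414 = 2.828, and Φ(0.868) = 0.807 (exact t-test: 0.804). Solving for 80% power gives 99 per arm by the normal formula and 99.1 by the exact t, which rounds up to 100. A literal power of 0.08 would need only 4 per arm, so the printed figure is read here as 0.80.

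**2. Adjusting for baseline abstinence.** The residual SD becomes √(1 − r²), so power = Φ(0.4 / (0.1414·√(1 − r²)) − 1.96). The equivalent unadjusted total is 200/(1 − r²).

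| r | power, 100 per arm | n per arm for 80% | equivalent unadjusted total |
|---|---|---|---|
| 0 (t-test) | 0.807 | 99 | 200 |
| 0.3 | 0.843 | 90 | 220 |
| 0.4 | 0.870 | 83 | 238 |
| 0.5 | 0.904 | 74 | 267 |
| 0.6 | 0.942 | 63 | 312 |

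**3. Chance imbalance in baseline abstinence.** The 95% range of the standardised difference between arms is ±1.96 × 0.1414 = ±0.28 SD. The t-test carries r times this into the estimate: 0.3 × 0.277 = 0.08 to 0.6 × 0.277 = 0.17 in units of d at the edge of that range, against a target of 0.4.

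**4. Institution in the t-test.** Under stratified blocks the true SE is √(1 − ICC) times the SE that the t-test uses. True type I error = 2[1 − Φ(1.96/√(1 − ICC))]. Unadjusted power = Φ(0.868/√(1 − ICC)). Adjusted power = Φ(2.828/√(1 − ICC) − 1.96).

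| ICC | type I error, unadjusted | power, unadjusted | power, adjusted | gain (points) |
|---|---|---|---|---|
| 0.01 | 0.0489 | 0.809 | 0.811 | 0.2 |
| 0.02 | 0.0477 | 0.810 | 0.815 | 0.5 |
| 0.05 | 0.0443 | 0.814 | 0.827 | 1.3 |
| 0.10 | 0.0388 | 0.820 | 0.846 | 2.6 |

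With both adjustments, r = 0.3 and ICC = 0.02 give power 0.850; r = 0.5 and ICC = 0.05 give 0.918.

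**5. Does the gain survive a bounded outcome?** In an illustrative simulation (longest run capped at 56 days, three abstinence strata, six sites, blocks of four, 2,000 replicates, r about 0.4), power was 0.70 for the t-test and 0.79 adjusted. Type I error was 0.042 and 0.043. With a weaker baseline relation (r about 0.25) and a larger effect, power was 0.88 against 0.90. The inputs are invented; the simulation shows direction only.

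**6. Institution in the SRRS model.** A site main effect is constant over time, so it acts on the intercept and not on the group-by-time slope being tested. In small simulations (for example 200 participants, six sites, visits at 2, 5 and 8 months), complete data gave the same interaction estimate with and without institution. SE ratios were about 0.99 to 1.00 with complete data and 1.007 with 20% of visits missing.

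**The case against.** The strongest defence is that nothing here is invalid. The t-test is unbiased over randomisation, and its type I error and confidence interval already allow for chance imbalance. It also matches the planning: the trial was sized on an unadjusted between-group d = 0.4, so adjustment adds power beyond the plan and does not repair a shortfall against it. The gain depends on an unknown r, and the simple formula assumes a homogeneous linear effect although many scores may sit at the 56-day ceiling. All of that stands, and it makes this a matter of efficiency.

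It does not remove the point. The test is spelled out in the article, so it is not a detail left to another document. The weighted GEE under Sensitivity analysis puts risk factors into the dropout weights and states no adjustment of the outcome for baseline abstinence or institution. The change-from-baseline outcome and the subgroups do not replace adjustment of the co-primary.

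Three stronger readings are tempting, and the documents support none of them:

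- **That leaving out institution lets imbalance bias the results.** Stratified blocks of four already nearly balance it; the effect is an SE slightly too large.
- **That the SRRS test suffers in the same way.** It tests a slope contrast, which a site main effect leaves almost untouched.
- **That baseline abstinence must dominate the outcome.** The protocol offers no figure from which a very high correlation could be derived.

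**Conclusion.** The point holds as a loss of precision on one co-primary. The plan uses an unadjusted t-test where a strongly plausible prognostic variable is already measured, and it leaves out the one stratification factor. Adjusting for baseline abstinence would lift power from about 0.80 to 0.84-0.94, equivalent to roughly 220-312 unadjusted participants in place of 200, if r lies between 0.3 and 0.6. The omission is certain; its size is not, because r is assumed. Institution matters little: 0.2-2.6 points of power for an ICC of 0.01-0.10, with an error rate slightly below 5%. For the SRRS interaction its effect is close to nil. A reader might infer that the abstinence result would be biased or its p-value unreliable; the design does not support that.

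**What to change.** Make the primary analysis of the longest abstinent run a linear model with robust standard errors (the 0-56 day bound makes constant variance doubtful) on group, institution and baseline abstinence from the primary drug. Report the adjusted mean difference with its 95% CI, and keep the t-test as supportive.

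Prespecify one coding of baseline abstinence. The 28-day count and the duration categories overlap heavily: anyone abstinent for over a month has 28 of 28 days, so the count varies essentially only within the under-1-month group. The three duration categories in the subgroup plan are a natural choice, provided the duration is dated from last use of the primary drug; Participant characteristics refers only to a drug.

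Adding institution to the SRRS model is optional, for consistency with the design.

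No new data are needed. Recruitment began in January 2015, and the protocol requires ethics approval and a registry revision for important modifications, so the cost is a documented amendment made before unblinding.
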